# Pre-Exposure Prophylaxis Integration Into Family Planning Services at Title X Clinics in the Southeastern United States: Protocol for a Mixed Methods Hybrid Type I Effectiveness Implementation Study (Phase 2 ATN 155)

**DOI:** 10.2196/18784

**Published:** 2020-09-25

**Keywords:** HIV, pre-exposure prophylaxis, implementation science, family planning services

## Abstract

**Background:**

Adolescent and young adult women (AYAW), particularly racial and ethnic minorities, in the Southern United States are disproportionately affected by HIV. Pre-exposure prophylaxis (PrEP) is an effective, scalable, individual-controlled HIV prevention strategy that is grossly underutilized among women of all ages and requires innovative delivery approaches to optimize its benefit. Anchoring PrEP delivery to family planning (FP) services that AYAW already trust, access routinely, and deem useful for their sexual health may offer an ideal opportunity to reach women at risk for HIV and to enhance their PrEP uptake and adherence. However, PrEP has not been widely integrated into FP services, including Title X–funded FP clinics that provide safety net sources of care for AYAW. To overcome potential implementation challenges for AYAW, Title X clinics in the Southern United States are uniquely positioned to be focal sites for conceptually informed and thoroughly evaluated PrEP implementation science studies.

**Objective:**

The objective of this study is two-fold: to evaluate multilevel factors associated with the level of PrEP adoption and implementation (eg, PrEP screening, counseling, and prescription) within and across 3 FP clinics and to evaluate PrEP uptake, persistence, and adherence among female patients in these clinics over a 6-month follow-up period.

**Methods:**

Phase 2 of Planning4PrEP (Adolescent Medicine Trials Network for HIV/AIDS Interventions 155) is a mixed methods hybrid type 1 effectiveness implementation study to be conducted in three clinics in Metro Atlanta, Georgia, United States. Guided by the Exploration, Preparation, Implementation, and Sustainment framework, this study will prepare clinics for PrEP integration via clinic-wide trainings and technical assistance and will develop clinic-specific PrEP implementation plans. We will monitor and evaluate PrEP implementation as well as female patient PrEP uptake, persistence, and adherence over a 6-month follow-up period.

**Results:**

Phase 2 of Planning4PrEP research activities began in February 2018 and are ongoing. Qualitative data analysis is scheduled to begin in Fall 2020.

**Conclusions:**

This study seeks to evaluate factors associated with the level of PrEP adoption and implementation (eg, PrEP screening, counseling, and prescription) within and across 3 FP clinics following training and implementation planning and to evaluate PrEP uptake, persistence, and adherence among female patients over a 6-month follow-up period. This will guide future strategies to support PrEP integration in Title X–funded clinics across the Southern United States.

**Trial Registration:**

ClinicalTrials.gov NCT04097834; https://clinicaltrials.gov/ct2/show/NCT04097834

**International Registered Report Identifier (IRRID):**

DERR1-10.2196/18784

## Introduction

Adolescent and young adult women (AYAW) in the Southern United States are disproportionately affected by HIV in comparison with AYAW residing in other regions [1]. Southern states account for nearly half of the new HIV diagnoses, despite having only 37% of the nation’s population [2]. In Atlanta, 4 metro counties (Cobb, DeKalb, Fulton, and Gwinnett) were identified as critical HIV hotspots in the Health and Human Services’ *Ending the HIV Epidemic: A Plan for America* [3]. Reducing HIV among women in the Southern United States in general, and Metro Atlanta specifically, is a priority.

Since approval of daily oral PrEP as an effective HIV prevention strategy [4], there has been wide-scale endorsement to bring PrEP to scale through dissemination and implementation efforts in the United States [5-7], but PrEP remains underutilized in women relative to need [8-10]. The first steps in PrEP adoption are ensuring that those who can benefit from PrEP are aware of it and ensuring PrEP is accessible in health care settings where they seek care [11,12]. However, there is low knowledge of PrEP among US women [13-18] and women’s health providers [19], although studies suggest that family planning (FP) providers are willing to prescribe PrEP once trained [19], and women are interested in taking PrEP once informed [20,21].

Anchoring PrEP delivery to health services such as FP clinics that AYAW already trust, access routinely, and deem useful for their sexual health is of great appeal. FP providers in areas with high HIV incidence are ideal potential PrEP providers because most (60%) AYAW utilize and trust FP providers for sexual health and preventative services [22]. Many are also important safety net sources of care for AYAW, particularly in states that did not expand Medicaid and are expected to offer HIV prevention services as part of quality FP [23].

However, PrEP has not been widely integrated into FP services in the United States. Our 2018 survey among individuals working in Title X clinics across the Southern United States revealed that the majority (approximately 80%) reported working in clinics that did not provide PrEP [24]. Our findings are in line with a 2015 national survey of FP providers in the United States, which reported low PrEP knowledge and use, especially in the South [19]. In addition, women have lower PrEP uptake and persistence than men [25], highlighting that significant implementation challenges exist among women.

Very few models exist that describe the organizational processes and strategies associated with successful integration of PrEP delivery in new clinic settings and none, to our knowledge, exists for FP clinics, including those supported by Title X funding. Despite the presence of clinical trial efficacy data for PrEP among both men and women, *real-world* effectiveness data on PrEP among women have only become recently available from studies among women in sub-Saharan Africa [26], thus lagging behind PrEP effectiveness research in men. Effectiveness-implementation hybrid designs are innovative implementation science approaches for more rapid *research to practice* translations. The hybrid type 1 design is a blended design that is ideally suited to test the effects of a clinical intervention on relevant patient outcomes in *real-world* settings (eg, PrEP uptake, adherence, and persistence among women) while gathering information on its implementation [27]. Given the aforementioned gaps in the literature on both effectiveness and implementation of PrEP among women in the United States, research employing a hybrid type 1 design is ideal for advancing the knowledge in this critical but understudied area and may inform future interventions to optimize PrEP delivery in this setting. Finally, maximizing the potential benefits of PrEP requires understanding the key provider- and patient-related steps in integrated PrEP delivery. These steps comprise the PrEP engagement cascade and have been proposed as a conceptual framework to identify and understand the key steps needed to maximize the benefits of PrEP [28-30]. However, there is a dearth of research exploring factors associated with these provider- and patient-related steps among women utilizing FP clinics in the Southeastern United States.

The Adolescent Medicine Trials Network for HIV/AIDS Interventions (ATN) is a research program that aims to defeat the rising HIV epidemic among adolescents and young adults in the United States. The overarching goal of the ATN is to increase awareness of HIV status in youth and, for those diagnosed with HIV, increase access to health care. The ATN develops and conducts behavioral, community-based, translational, therapeutic, microbicide, and vaccine trials in youth who are at risk for or living with HIV, with a focus on the inclusion of minors. Our study is funded as part of the ATN (ATN 155). The combined findings and resulting tools and trainings will be valuable for PrEP integration in Title X–funded or similarly structured FP clinics and to inform future interventions to optimize PrEP delivery for AYAW. Phase 2 of Planning4PrEP was directly guided by phase 1 of the study; review phase 1 protocol paper for complete details [31]. In this paper, we describe only the research protocol for the phase 2 study. The objective of this study is to evaluate multilevel factors associated with the level of PrEP adoption and implementation within and across 3 FP clinics and to evaluate PrEP uptake, persistence, and adherence among female patients in these clinics over a 6-month follow-up period.

## Methods

### Study Design

This study is a mixed methods hybrid type 1 effectiveness implementation study with two key objectives. Objective one is to evaluate factors associated with clinic-level PrEP adoption and implementation at three FP clinics. This objective will be measured both quantitatively and qualitatively. Quantitative data include clinic-level aggregate data obtained via chart abstraction, staff-level data obtained via a web-based survey, and patient-level data collected via interviewer-assisted exit surveys. In addition to the web-based survey, staff participants will also take part in key informant interviews and focus groups. Objective two is to evaluate the effect of PrEP integration on PrEP uptake, persistence, and adherence among female patient participants over a 6-month period. This objective will be measured via a prospective cohort study of 300 PrEP-eligible women across all three clinics. To characterize each step in the PrEP cascade, within this cohort, we aim to recruit women who may benefit from PrEP (as determined via HIV risk assessment by the patient or provider), regardless of whether PrEP was prescribed.

Both objectives directly correlate to different stages of the Exploration, Preparation, Implementation, and Sustainment (EPIS) framework (Figure 1). Methods pertinent to objective one fall under preparation, implementation and sustainment phases, whereas methods pertinent to objective two fall under the implementation and sustainment phases. Importantly, objective two methods are essential for better understanding real-world PrEP effectiveness among women in the United States. Secondary outcome measures among staff participants will be mapped to the Consolidated Framework for Implementation Research (CFIR) framework.

**Figure 1 figure1:**
[figure not shown]
Pre-exposure prophylaxis implementation and evaluation process at three Atlanta Title X clinics including a federally qualified health center clinic, specialized family planning clinic, and hospital-based family planning clinic. CCT: Clinic Change Team; FP: family planning; PrEP: pre-exposure prophylaxis.

### Theoretical Frameworks

#### EPIS Framework

The EPIS framework [32] is a phased, multilevel (ie, clinic and provider and staff-level) approach to conceptualizing implementation research that provides both structure and a process to implementation across 4 distinct stages. *Exploration*, the first stage, was assessed in the first phase of this study [31]. The next step, *preparation*, involves bringing together relevant stakeholders in a planning process to support effective implementation and includes developing a proposed plan to address barriers (eg, through clinic-wide PrEP trainings and capacity building with local PrEP technical assistance providers). The *implementation* stage begins after training or when other system changes are required for the PrEP end. When implementation reaches normalized operations (eg, a clinic can onboard a new provider and ensure that they are prepared to screen and provide PrEP), *sustainment* begins. This study will thoroughly evaluate EPIS stages from *preparation* to the early *sustainment* stage.

#### CFIR

Using the CFIR framework [33], we will assess which inner and outer contextual factors (barriers and facilitators) influence the level of adoption of PrEP services in Title X clinics serving women in the Southern United States. The CFIR provides a menu of constructs that have been identified as important for implementation success [33]. The CFIR captures the complex, multilevel nature of implementation and posits that successful implementation of a new innovation (PrEP delivery in FP clinics) will likely require the use of multiple strategies (eg, training, technical assistance, and an internal champion) at multiple levels of the implementation context. The CFIR comprises 39 constructs organized into 5 domains (intervention characteristics, outer setting, inner setting, characteristics of individuals, and process).

### Consent and Institutional Review Board Approval

Given the various types of study participants (patients and clinic staff), phase 2 of this study was divided into two parts for logistical and institutional review board (IRB) purposes. Both parts have been reviewed and approved by the Emory University IRB (IRB# 00107692 and 00111612) and the University of North Carolina at Chapel Hill IRB (IRB# 18-2442 and 19-1784).

Written consent for the clinic staff focus groups, clinic staff web-based surveys, clinic patient surveys, and cohort study will be obtained for all willing participants before participation. Among the web-based survey participants, written consent is asked within the survey. These survey responses are de-identified to protect participants’ privacy. Staff participants indicate interest in a follow-up qualitative interview during the consent process. Verbal consent is obtained over the telephone before the start of the qualitative interview.

### Participants

#### Clinic Staff

Clinic staff participants may include any staff, provider, or administrator employed at any of the three clinics in the phase 2 study. Across all three clinics, at each evaluation time point, there will be up to 100 staff surveys, 45 staff key informant interviews, and 20 staff focus group participants. Cross-sectional enrollment at each evaluation time point rather than a longitudinal assessment of select staff over the entire study period was selected given the staff turnover.

#### Clinic Patients

Patient participants include self-identified, female patients receiving care by a provider on the day of assessment at any of the three clinic sites. As the three clinics see women of varying ages, we will not restrict to younger ages. This will allow for a comprehensive assessment of PrEP implementation in these clinics, across their patient population, and identification of age-specific associated factors. Patient participants who complete the one-time patient exit survey must be aged 13 to 45 years, able to speak and understand English, not self-reported HIV positive, and have completed a visit at one of the three clinics on the day of survey consent. Patient exit surveys will occur approximately once quarterly for up to 9 time points (depending on onset of implementation phase), with up to 60 participants across all three clinics per time point. Patient participants may complete a survey at more than one time point, but their responses will not be linked.

#### Cohort Patients

Patient participants enrolled into the cohort component of this study must meet additional inclusion and exclusion criteria. These participants must have been seen for a patient visit in one of the three implementation clinics during the preceding 60 days and identified as a PrEP candidate based on HIV testing and risk assessment. In addition, they must not be currently enrolled in an HIV vaccine trial, have not been on PrEP for 7 or more consecutive days in the past, not be currently receiving PrEP care outside of the three clinics, and not be currently participating in another PrEP or candidate PrEP study. This cohort has a target enrollment of 300.

### Recruitment

#### Clinic Staff

All clinic staff, including providers and administrators, who are part of FP services at each clinic site will be approached for participation by study staff. Clinic staff will be invited via email to participate in staff surveys. As part of the survey, individuals will be asked if they are interested in potentially participating in key informant interviews. Among those who indicate their willingness, a select group within each clinic will be purposefully selected and invited via email or phone to participate in key informant interviews. Finally, individuals comprising the Clinic Change Team, including the designated PrEP Champion, will be invited via email to participate in focus groups. Clinic leadership at each clinic site will select a PrEP Champion as well as a Clinic Change Team.

#### Clinic Patients

Clinic patient participants will be recruited by trained study staff. Specifically, study staff will attend clinic on days when FP patients are being seen and will review the daily FP clinic schedule with a designated FP clinic staff member to identify individuals to approach for recruitment (see eligibility criteria). Study staff will approach potentially eligible patients and invite them to participate in the exit survey immediately following their provider visit.

#### Cohort Patients

Cohort patient participants will be recruited for the study using flyers and clinic staff referrals. Clinic staff will refer PrEP-eligible women who meet the eligibility criteria and agree to be contacted for a potential research study directly to study staff. In addition, clinic staff will distribute flyers to potential participants with study staff contact information, and study staff will be present in the clinics during regular intervals to facilitate on-site recruitment.

### Incentives

All participants (clinic staff and patients) will be offered compensation for their time.

### Data Collection

#### Clinic Staff

Aggregate of quarterly clinic-level data will be collected via clinic medical chart abstraction over the course of the study.

Quantitative and qualitative data will be collected for staff participants at three time points (approximately annually). Quantitative data will be collected via a web-based survey [31], taking approximately 20-30 min to complete. For the staff survey, the study staff will distribute the survey link via clinic email addresses. Qualitative data collection includes key informant interviews and focus groups. Key informant interviews will last approximately 60 min and will occur either in person or over the telephone. Staff participants who comprise the Clinic Change Team, which includes clinic staff and administrators who participated in PrEP implementation trainings and are involved in PrEP implementation in their clinics, will participate in in-person focus groups. Focus groups are expected to last 60-90 min. Trained study staff will conduct key informant interviews and focus groups, with at least two study staff facilitating focus groups (one as facilitator and one as a note taker). All interviews and focus groups will be audio recorded and sent for professional transcription.

#### Clinic Patients

Clinic patient participants will complete a brief (less than 10 min) interviewer-assisted patient exit survey following a visit at one of the three FP clinics. Clinic patient participants will be recruited approximately quarterly.

#### Cohort Patients

Data relevant to cohort patient participants will encompass medical chart review, interviewer-administered surveys, audio computer-assisted self-interviews, and pharmacologic and laboratory data. Data for cohort patient participants will be collected by trained study staff at the baseline, 3-month, and 6-month follow-up visits, with the allowance for interim visits as needed.

### Quantitative Data Analysis

#### Sample Size

The prospective cohort study will attempt to enroll up to 300 PrEP-eligible women across three clinics. Sample sizes pertaining to clinic staff and clinic patient participants were not chosen to yield a specified level of statistical power for hypothesis testing or to provide a specific level of precision for estimation of a target estimand. However, based on a sample size of 300, the study will provide the ability to estimate the percentage of PrEP-eligible women who are willing to initiate PrEP at baseline within a margin of error of approximately 4.5% (assuming a true uptake percentage of 20%). If instead only 150 participants are enrolled, the margin of error increases to 6.4%. If the actual uptake is lower than assumed, the margin of error will be less than stated.

As this is the first study of its kind focusing on the components of the PrEP cascade in this population and estimates for uptake of PrEP are not available for women seeking care in FP clinics in the Southern United States, the distribution of patients who achieve each step of the PrEP cascade is not well understood. As a result, the quantitative data analysis objectives for the study are not powered for any specific hypothesis testing aim or to achieve a particular level of precision for a specific target estimand. However, based on a sample size of 300, the study will provide 70% power or more to detect a 12% difference in PrEP uptake between race groups (binary) provided the sample size distribution between the two race groups is not more imbalanced than 2:1, assuming a true uptake percentage in two groups of 15% and 27%, and based on a 5% significance level for the test.

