**Cohort patients**		
	PrEP uptake	Participant who receives a PrEP prescription at the baseline visit, fills their prescription, and self-reports initiating PrEP
	PrEP persistence	Participant who attends at least one follow-up visit and has a documented pharmacy refill of PrEP medication at least once during each 3-month interval
	PrEP adherence—hair sample	Average tenofovir concentration measured using a small hair sample (ng/mg); percentage of participants with adherence level consistent with 7 doses per week (≥0.0370 ng/mg) [34,35]
	PrEP adherence—blood sample	Percentage of participants with dried blood spot tenofovir concentration≥1250 fmol/punch
	PrEP adherence—urine sample	Percentage of participants with tenofovir detected by urine immunoassay
	PrEP adherence—self-report	Percentage of participants reporting no missed doses in the past 7 days; percentage of participants reporting very good or excellent adherence (5 or 6 on a 6-level Likert scale) [36] in the past 30 days; percentage of participants who self-report adherence of 90% or higher
	PrEP adherence—pharmacy fill	Percentage of participants with 80% adherence by medication possession ratio defined as the number of dispensed pills divided by the number of days since starting PrEP [37,38]

^a^PrEP: pre-exposure prophylaxis.

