#### Statistical Analysis

For quantitative outcomes defined based on chart abstraction (HIV testing, HIV risk assessments, and PrEP prescriptions) and clinic patient exit surveys (HIV prevention counseling, HIV prevention counseling including information about PrEP), we will compute the proportion of patients meeting the outcome definition (eg, portion who received an HIV test) along with 95% confidence intervals. For analyses based on clinic patient exit surveys, data from all exit surveys will be included in the statistical analysis.

For quantitative outcomes defined for cohort patients, all data will be included in analyses for all patients from enrollment until completion of the study or until the patient discontinues participation or becomes lost to follow-up. For the PrEP uptake and PrEP persistence outcomes, the proportion of patients meeting the outcome definition along with 95% confidence intervals will be computed. Association analyses will be performed using mixed logistic regression models to determine whether outcomes are associated with patient-level characteristics such as age, race, education level, and relationship status.

For PrEP adherence outcomes, data from all patients who initiate PrEP at their baseline visit will be included in the analyses. The proportion of patients meeting each PrEP adherence outcome definition along with 95% confidence intervals will be computed at the 3- and 6-month post baseline time points. Analyses will be performed using mixed logistic regression models to determine whether adherence outcomes are associated with patient-level characteristics such as age, race, education level, and relationship status and whether adherence rates change over the 6-month observation period. Analyses will be performed that also incorporate data from patients who initiate PrEP after their baseline visit. Agreement between the different PrEP adherence outcome measures will also be assessed using standard methods (eg, weighted kappa statistic).

Before the analysis of quantitative data, a comprehensive statistical analysis plan will be developed and finalized. Primary and secondary study outcomes and statistical analysis methods will be described in full detail in the study’s statistical analysis plan. This plan will be accessible on ClinicalTrials.gov once available.

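### The 70% power floor for the race comparison of PrEP uptake does not hold at the 2:1 split it names: with a two-sided 5% pooled z-test, power there falls to about 65%

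*Protocol article*

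**What the plan says.** The power statement is in the protocol article, Quantitative Data Analysis, under Sample Size. It has these parts:

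- Size: "based on a sample size of 300, the study will provide 70% power or more".
- Power and comparison: "70% power or more to detect a 12% difference in PrEP uptake between race groups (binary".
- Condition on the split: "provided the sample size distribution between the two race groups is not more imbalanced than 2:1".
- Rates: "assuming a true uptake percentage in two groups of 15% and 27" (per cent).
- Level: "based on a 5% significance level for the test".

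The statement does not name the test, say whether it is one- or two-sided, or say which race group is larger or which has the lower uptake. Just before it, the same paragraph says that the quantitative objectives are not powered for any particular hypothesis test. Under Statistical Analysis, race is one of several example covariates for uptake: "Association analyses will be performed using mixed logistic regression models".

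**The concern.** A power of 70% or more, subject only to a limit on imbalance, is a guaranteed minimum. It must therefore hold at the limit itself, 100 against 200. For two proportions with unequal variances, power at a 2:1 split also depends on which group is the smaller. As the article leaves that open, the minimum must hold in both orientations. If it does not, the article's only stated power figure is somewhat optimistic at the edge of its own condition. A reader weighing a null race result would then credit the comparison with a little more power than the design gives.

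**Working it through.** **Inputs, all from the Sample Size section except where marked.** Total 300; rates 0.15 and 0.27, so the difference is 0.12; most extreme split 100/200; 5% level. *Assumption:* two-sided, z = 1.96. This is the usual convention and agrees with the 95% confidence intervals planned elsewhere. No dropout is applied, because uptake is tied to the baseline prescription: "Participant who receives a PrEP prescription at the baseline visit, fills their prescription, and self-reports initiating PrEP".

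**Neighbouring figures first.** The margin of error at 20% uptake is 1.96 × √(0.2 × 0.8 / 300) = 4.5 points, and with 150 women it is 6.4 points. Both match the article.

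**Pooled z-test.** Power = Φ[(0.12 − 1.96 × SE0) / SE1], where SE0 = √[p̄(1 − p̄)(1/n1 + 1/n2)] and SE1 = √[p1(1 − p1)/n1 + p2(1 − p2)/n2]. Group 1 has 15% uptake and group 2 has 27%.

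- *1:1 (150/150).* p̄ = 0.21, SE0 = 0.0470, SE1 = 0.0465. Power = Φ(0.598) = 72.5%, so the floor is met.
- *2:1, 15% group smaller (100/200).* p̄ = (100 × 0.15 + 200 × 0.27)/300 = 0.23, SE0 = 0.0515, SE1 = 0.0475. Power = Φ(0.399) = 65.5%.
- *2:1, 27% group smaller (200/100).* p̄ = 0.19, SE0 = 0.0480, SE1 = 0.0511. Power = Φ(0.506) = 69.35%.

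The last value is close to 70% and may be where the stated figure came from. It is only one of the two orientations.

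**Unpooled z-test.** Power = Φ(0.12/SE1 − 1.96). With the 15% group smaller this is Φ(0.564) = 71.4%. With the 27% group smaller it is Φ(0.390) = 65.2%.

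**Wald test of the log odds ratio.** The log odds ratio is ln(0.27/0.73) − ln(0.15/0.85) = 0.740. Its standard error is √[1/(n1 p1(1 − p1)) + 1/(n2 p2(1 − p2))].

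- 15% group smaller: SE = 0.322, power = Φ(0.740/0.322 − 1.96) = 63.2%.
- 27% group smaller: SE = 0.300, power = 69.4%.

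**All two-sided results at 2:1**

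| Method | 15% group smaller | 27% group smaller |
|---|---|---|
| Pooled z | 65.5% | 69.35% |
| Pooled test, exact enumeration | 66.2% | 69.4% |
| Unpooled z | 71.4% | 65.2% |
| Log-odds-ratio Wald | 63.2% | 69.4% |
| Arcsine | 68.0% | 68.0% |
| Likelihood ratio, exact enumeration | 68.3% | 68.4% |
| Fisher's exact | 64.8% | 66.6% |
| Continuity-corrected z | 59.5% | 64.0% |

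No row reaches 70% in both columns. The best worst case is about 68%.

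**Where 70% stops holding (pooled z, 15% group smaller).** 72.5% at 1:1; 70.5% at 1.4:1 (125/175); 69.7% at 1.5:1 (120/180); 67.7% at 1.75:1; 65.5% at 2:1.

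**Sensitivity to sidedness.** A one-sided 5% pooled z-test at 2:1 gives 77.1% and 78.9%. Across the pooled, unpooled, log-odds-ratio and arcsine versions, the one-sided range at 2:1 is about 74% to 81%.

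**The case against.** Several points on the other side have weight.

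*The result rests on unstated choices.* This stands in part. A one-sided 5% test would satisfy the floor in both orientations. But the article gives no direction for the race difference, and one-sided power of 77% to 79% would be an odd thing to report as 70% or more. Two-sided is the likelier reading, but it remains an assumption. Leaving the test to the SAP is acceptable in an article. The difficulty is a stated number that the usual calculations do not deliver.

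*In one orientation the figure is nearly right or right.* True: about 69% for the pooled test with the 27% group smaller, and 71.4% for the unpooled test with the 15% group smaller. Neither test holds up when the groups are swapped.

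*The comparison is illustrative.* This stands and limits the importance. The primary objectives are descriptive, the 300 was not derived from this calculation, and the same paragraph disclaims powering for any hypothesis test.

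A reader might also infer three stronger things that the documents do not support:

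- *That power at 2:1 is below 70% under every test and orientation.* The 71.4% shows otherwise. The claim fails as a floor, not in every cell.
- *That the shortfall is definitely about 7 points, because logistic regression is planned.* The article never ties the power figure to that model. Seven points is the Wald result only.
- *That leaving out power at 150 women is an error.* The article says "If instead only 150 participants are enrolled, the margin of error increases to 6.4" (per cent), but that concerns the margin of error. The power claim is expressly conditional on 300.

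**Conclusion.** The statement is wrong as written, to a minor degree. With 300 women, 15% against 27% and an assumed two-sided 5% test, 70% is not a floor at 2:1. In the less favourable orientation the shortfall is 4.5 points with the pooled z-test (65.5%), 4.8 with the unpooled z-test (65.2%) and 6.8 with the log-odds-ratio Wald test (63.2%). The most favourable method is still almost 2 points short. If a one-sided test was meant, the floor holds, and the sentence should say so.

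This does not show that the study is too small for its purpose. No enrolment target, outcome definition, planned analysis or decision rule depends on the figure, and a null race result would call for caution at 65% or at 70%.

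**What to change.** Change one sentence in the Sample Size section, in one of two ways, naming the test and its sidedness in either case:

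1. Restate the figure: *with 300 women and a two-sided 5% pooled z-test, power to detect 15% against 27% is about 72% at a 1:1 split, falling to about 65% at 2:1 in the less favourable orientation.*
2. Keep 70% and limit it to an imbalance of about 1.4:1 or less under that same test. A limit of 1.5:1 would not do, since pooled power there is 69.7% with the 15% group smaller. The 1.4:1 limit belongs to the pooled z-test and should not be carried over to another test unchecked.

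The authors may add, for information, that with 150 women the pooled z-test has about 37% to 43% power at 2:1 and 44% at 1:1. This is optional.

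The cost is a slightly less favourable stated figure, or a narrower condition on it. Enrolment, design and analysis do not change.
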